## Abstract

**Background:**

Type 1 diabetes is a serious, life-long condition which causes major health, social and economic burden for children, their families and the community. Diabetes management involves strict adherence to a complex regimen, and poor management and non-adherence are a persistent problem among children. Parent-child interactions and parenting have been identified as crucial points of intervention to support children’s health and emotional well-being, yet few parenting interventions have been developed or evaluated for parents of young children. This paper describes a randomised controlled trial of a brief, group-based parenting intervention for parents of young children (2-10 years) with type 1 diabetes compared against care as usual (CAU).

**Methods/design:**

Families will be randomised to either Positive Parenting for Healthy Living Triple P or CAU. Positive Parenting for Healthy Living Triple P involves 2 × 2 h group sessions. Outcomes will be assessed via parent and child questionnaire, home observations and blood glucose monitoring at baseline, 1-month and 6-months post-intervention. Primary outcomes will be parent- and child-reported parenting behaviour, parent-reported child behaviour and adjustment, and parent-reported child quality-of-life. Secondary outcomes will include parental self-efficacy with diabetes management, illness-specific and general parenting stress, parent-reported child illness behaviour, family quality-of-life, observed parenting and child behaviour, and child’s illness control.

**Discussion:**

The theoretical background, study hypotheses, methods and planned analyses are discussed.

**Trial registration:**

Australian New Zealand Clinical Trials Registry: ACTRN12613001281785. Registered 20 November, 2013.

## Background

It is estimated that, on an annual basis, 70,000 children under 15 years of age develop type 1 diabetes worldwide [1], and the incidence is rising globally with an estimated overall annual increase of approximately 3 % [2]. Type 1 diabetes is a chronic condition which requires constant attention and monitoring. Day-to-day management involves frequent blood glucose monitoring, multiple insulin injections, and regulation of carbohydrate intake and physical activity to prevent short-term and long-term complications [3]. Despite the problems associated with poor management, non-adherence to diabetes treatment regimens is a persistent problem, and adherence tends to be worse than for other chronic health conditions [4]. Rates of adherence for insulin injections have been reported to range from 20 to 80 %, about 65 % for dietary recommendations, 57 to 70 % for blood glucose monitoring, and 19 to 30 % for adherence to exercise regimens [5]. Research has established links between poor illness management and children’s psychological health [6], and behaviour [7], which may in turn contribute to poorer diabetes control [8].

Parents play an important role in management of diabetes, especially with young children when parents assume complete responsibility for illness management. Parents of children with type 1 diabetes need to integrate general parenting tasks, such as helping children manage their emotions and providing them with appropriate social and play experiences, with diabetes-specific tasks, such as maintaining optimal blood glucose levels and responding quickly and effectively to emergency situations (e.g., extreme hypoglycaemia). Management of type 1 diabetes in young children requires them to cooperate with their treatment regimen, yet research has demonstrated that children with diabetes tend to report more behavioural, adjustment and emotional problems compared to healthy children [9–11].

The link between ineffective parenting and child behaviour problems [12–15] has been clearly established, and it plays an important role in parenting children with diabetes [16]. Positive parenting behaviours characterised by positive, confident and effective parenting have been associated with better management of diabetes [17], better child adjustment [17], and diabetes-related quality of life [18]. Parenting and family factors also play an important role in child health outcomes. Factors such as positive and confident parenting have been linked with good diabetes control and treatment adherence in children [17, 19]. On the other hand, inconsistent and ineffective parenting practices (for instance, permissive parenting and overprotection) have been associated with poor metabolic control and adherence [20, 21].

In spite of the clear links between parenting and child outcomes in the context of type 1 diabetes, a recent review highlights the scarcity of parenting interventions for this population [22]. Most existing interventions are educational in nature, focusing narrowly on the child’s medical management rather than on the broader psychosocial context [23–26], despite evidence that behavioural interventions are more effective than educational interventions [27]. Although data on effectiveness of parenting interventions in children with type 1 diabetes is limited due to a relative dearth of well-controlled studies in this area, existing parenting interventions have demonstrated some potential for effectiveness in improving responsibility sharing and child cooperation in diabetes management, child behaviour difficulties, parental behaviour, parents’ psychological distress and child health outcomes [22]. Interventions aimed at reducing family conflict and improving family communication have also led to improved adherence rates and health outcomes for adolescents with diabetes [28–30].

Given the increasing prevalence of the condition, the reported difficulties with illness management, the higher levels of child behavioural and emotional problems and the lack of evidence based interventions, there is a critical need to establish the efficacy of parenting interventions for parents of children with type 1 diabetes so that evidence-based parenting programs can be made available to families. Parenting interventions which aim to improve positive parenting practices may lead not only to better general child behavioural and emotional outcomes, but also better child health outcomes. Interventions which focus on parental skills, parenting efficacy and effective self-regulatory skills can assist parents to manage their child’s condition more effectively through developing better daily routines and encouraging their child’s involvement in illness management [31].

## Application of triple P in type 1 diabetes

The Triple P - Positive Parenting Program is an established, evidence-based system of parenting intervention [32]. It is based on social learning principles, cognitive-behavioural and developmental theory, and aims to treat and prevent child behavioural and emotional difficulties by improving the skills, knowledge and confidence of parents, improving communication between parents, and reducing parental stress [33, 34]. Several meta-analyses have provided solid evidence that the program is effective in improving child behaviour and parenting outcomes [35–38]. Triple P has been adapted for and found to be effective in different populations such as parents of children with a disability [39], Indigenous families [40], and parents going through a divorce [41], among others.

To date there have been limited evaluations of Triple P with parents of children with a chronic health condition. Westruppet al. (2014) evaluated a 10-session individually delivered program (Standard Triple P) for parents of children with type 1 diabetes, aged 4–12 years. Parents randomly allocated to the intervention condition reported improved parent mental health, parenting skills and family functioning at 3 months post-intervention, but no effects were seen on child mental health, child behaviour and glycaemic control at either 3- or 12-month follow-up. Subgroup analyses revealed that the program was effective in improving child behaviour in children with pre-existing internalizing and externalizing behaviour problems, with moderate-to-large effect sizes at 3 months post-intervention [42].

Another study by Doherty, Calam and Sanders [43] evaluated whether the Self-Directed Teen Triple P workbook (10 modules) plus a chronic illness tip sheet could reduce diabetes-related family conflict and parental stress in parents of adolescents (aged 11-17 years) with type 1 diabetes. Participants in the intervention group reported significantly improved diabetes-related family conflict problems after participating in Triple P compared to those in usual care. However, no significant difference was found between groups for parental stress [43].

A program with a generic condition approach was chosen for this study because primary care and community health services are more likely to care for children with a range of chronic health conditions; thus, a program addressing the common issues and concerns across different health conditions (with examples tailored for specific condition groups) may be more helpful from a large-scale population dissemination perspective. This is the first randomized controlled trial to test the efficacy of the *Positive Parenting for Healthy Living* program for parents of children with type 1 diabetes. Given the scarcity of parenting interventions for this population, and demonstrated efficacy of the program in the asthma and eczema context, the program may have the potential to improve parent and child outcomes in the type 1 diabetes population.

## Aims and hypotheses

This study aims to use multi-informant assessment to test the efficacy of *Positive Parenting for Healthy Living* for parents of children with type 1 diabetes. Specifically, the primary outcomes will be: (i) parent self-reported parenting behaviour; (ii) child-reported parenting behaviour; (iii) parent-reported child behaviour and adjustment; and (iv) parent-reported child health-related quality-of-life. Secondary outcomes will be: (i) child’s metabolic control (as indicated by HbA1c and within-range blood glucose readings); (ii) parents’ self-efficacy with diabetes management; (iii) parent-reported illness-specific child behaviour problems; (iv) parent-reported family quality-of-life; (v) parents’ diabetes-related stress and (vi) general parenting stress; (vii) observed parenting behaviour; and (viii) observed child behaviour. We hypothesise that, compared to a CAU group, the intervention group (INT) will show significantly greater improvement on each outcome measure at (a) post-intervention and (b) 6-month follow-up.

## Method

### Approach and methodology

This research will evaluate a brief skills-training program for parents of children with type 1 diabetes in a randomised controlled trial comparing the parenting intervention against care as usual. A care as usual group was chosen as the comparator to allow for evaluation of the intervention against current practice. The CONSORT guidelines for randomised controlled trials will be used.

### Design

The study is a 2 (Triple P vs CAU) × 3 (time: pre-test, post-test, 6-month follow-up) design superiority trial with 1:1 allocation ratio.

### Ethics

Ethical approval has been obtained from the Queensland Children’s Health Services Human Research Ethics Committee (HREC/14/QRCH/1) and the University of Queensland Behavioural and Social Sciences Ethical Review Committee (2013001357). This trial has been registered with the Australian and New Zealand Clinical Trials registration: ACTRN12613001281785 (Appendix A: Table 2). Ethics amendments approval will be sought before any further modification to the protocol is made. Any further approved changes to the protocol will also be updated on the trial registry.

### Participants

Participants will be 60 families of 2–10 year old children with type 1 diabetes, recruited through primary care settings, paediatric specialists, specialist clinics at major Brisbane hospitals, and through targeted mail-out and media campaigns. Diagnostic confirmation of the child’s diabetes will be sought from the child’s treating diabetes team.

#### Inclusion and exclusion criteria

Parents of children aged 2-10 years with type 1 diabetes will be recruited. Parents must be concerned about their child’s behaviour, emotions, or illness management to be included in the study. Parents will be excluded if: (i) the child has a disability, including language and speech impairment; (ii) parents are currently seeing a professional for the child’s behaviour difficulties; (iii) the child has been diagnosed with type 1 diabetes for less than three months; (iv) parents are currently receiving psychological help or counselling; (v) parents are intellectually disabled; or (vi) parents do not read and understand English.

#### Recruitment

Participants will primarily be recruited through in-clinic recruitment at the Endocrinology Clinic of the Lady Cilento Children’s Hospital (Brisbane, Australia). All parents with a child between 2 and 10 years of age with a diagnosis of type 1 diabetes listed on the hospital database will be mailed a letter of invitation to participate in the study. Parents can register their interest in the study by phone, email, or on the study website. Parents will also be encouraged to discuss any questions or concerns regarding participation with a member of the research team who will be present in the clinic.

Recruitment brochures and posters will also be distributed and displayed at GP clinics and paediatrician offices across the Greater Brisbane area. In addition, information about the study will be emailed to Brisbane schools for inclusion in school newsletters. The same information will also be available through advertisements posted on websites and social media pages of relevant organisations, such as Diabetes Queensland and the Juvenile Diabetes Research Foundation, Australia. Other sources of recruitment include advertisements in the University of Queensland staff newsletter and posts on diabetes-specific parenting forums.

Interested parents will be assessed for eligibility and enrolled in the study by the study coordinator. Following eligibility screening, both parents will complete self-report assessment measures as relevant, and a home observation and child report measures will also be completed. All parent and child participants will receive information and consent forms detailing the project, and consent will only be gained once participants have had an opportunity to address any concerns or questions. Consent will also be sought to contact the family’s diabetes team to obtain confirmation of the child’s diagnosis and details of illness status. Participation will be completely voluntary and participants will be free to withdraw at any time. No further data will be collected from participants who actively withdraw from the study. Any families needing additional help at follow-up will be provided with appropriate referrals to community-based professional services. Participants will be provided with contact details for the research team and ethics committee should they need to report any adverse events. Detailed progress reports will be submitted to the relevant ethics committees annually, and any adverse events will be reported within 72 h.

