##### Diabetes team report

The target blood glucose ranges for each child will also be obtained from their diabetes team at the time of their enrolment in the study, which will be used to check for in- and out-of-range readings. Glycosylated haemoglobin (HbA1c) levels will be obtained from the child’s diabetes team at the time of their routine medical review. HbA1c levels provide an indication of an individual’s average blood glucose concentration over the previous 3 months, and are considered the best marker of longer-term diabetes control. As a reference point, the HbA1c levels are usually between 4.0 to 6.0 % in individuals who do not have diabetes. In Australia, HbA1c targets for children and adolescents with type 1 diabetes are <7.5 % [55, 56]. HbA1c levels of 8.0 % or above may indicate that tighter control of blood glucose levels is required. Similar to blood glucose values, change in HbA1c values will provide us with an indication of whether the intervention has an effect on longer-term glycaemic control.

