### Statistical analyses

Prior to conducting the main analyses, data will be screened for distributional assumptions (e.g., univariate and multivariate normality, outliers, and multi-collinearity) as well as inter- and intra-measure consistency. Preliminary analyses will also investigate whether the study groups differ on any demographic or clinical characteristics at baseline. Group differences in baseline characteristics will be examined via linear (for continuous outcomes) and logistic (for categorical outcomes) regression models. It is anticipated that the groups will not differ at baseline due to randomisation to study conditions. If baseline group differences are detected, we will investigate and report the extent to which the results from the planned analyses described below are altered, when these differences are statically controlled. For missing data points, an analysis of missing data will be conducted (see paragraph below on missing data) and imputation methods will be considered [65]. Data analysis will follow the intention-to-treat principle, which means that the study population subjected to the analysis will consist of all randomised individuals.

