### Missing outcome data

In any longitudinal design it is inevitable that some individuals will drop out from the study. For this reason, the study sample size was calculated to allow for a dropout rate of 16 %. Assuming that the complete data may only be available for 84 % of families at the end of the study, intention-to-treat analysis will be applied to allow all randomized families to be included in the analyses. Missing data will be accommodated via implementation of full information maximum likelihood analysis (FIML). This approach yields intention-to-treat estimates consistent with what would be expected if there were no missing data, given that the assumptions of either Missing Completely at Random (MCAR) or Missing at Random (MAR) are met [65].

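### Read literally, the withdrawal rule also ends collection of routine HbA1c, which the diabetes team could still supply without study contact

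*Protocol article*

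**What the plan says.** The rule is one sentence in the Recruitment section: "No further data will be collected from participants who actively withdraw from the study". No exception or intermediate level of withdrawal is described.

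HbA1c is part of the first secondary outcome, metabolic control (Aims and hypotheses). Under Diabetes team report the article says: "Glycosylated haemoglobin (HbA1c) levels will be obtained from the child’s diabetes team at the time of their routine medical review". Access to the team rests on the family's agreement, also set out under Recruitment: "Consent will also be sought to contact the family’s diabetes team to obtain confirmation of the child’s diagnosis and details of illness status". Both arms keep their regular diabetes care throughout (Randomisation; Care as usual condition).

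On the analysis, the Statistical analyses section says that "the study population subjected to the analysis will consist of all randomised individuals". Missing outcome data repeats that "intention-to-treat analysis will be applied to allow all randomized families to be included in the analyses", handles missing values by FIML, and makes the validity of this conditional on data being missing completely at random or at random. The same section notes that "the study sample size was calculated to allow for a dropout rate of 16" per cent.

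**The concern.** Most of the trial's data need the family's effort: questionnaires, home visits, meter downloads. HbA1c does not. It is measured in routine care and passed on by the diabetes team, so for most families that stop taking part the value will normally still exist. A family that is tired of questionnaires or of being filmed at home may have no objection to the team continuing to pass on HbA1c, but the article gives it no stated way to say so.

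At stake is avoidable missing data in the measure that the article itself treats as the best marker of longer-term control. An HbA1c value reflects roughly the preceding three months (Diabetes team report). A change that begins after the last recorded value is therefore invisible in the data the trial holds. If families withdraw because of such a change, the missing-at-random assumption fails and FIML cannot repair the loss. A later analysis plan can test sensitivity to that, but it cannot supply values that were never collected.

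**Working it through.** **1. Does the rule reach HbA1c?** The Recruitment sentence covers any further data from a participant who actively withdraws from the study. HbA1c comes from the team, but it is data on the participant, obtained under the family's consent. Nothing in Diabetes team report exempts it. Read literally, collection of HbA1c ends as well. The sentence does not mention families who miss sessions, skip a questionnaire or lose contact, so the rule does not reach them.

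**2. What remains in the analysis?** All randomised families are analysed and FIML uses whatever was recorded. For a family that withdraws after the post-intervention assessment, baseline and post-intervention values stay in and only the 6-month value is missing.

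**3. How much missing data does the plan allow for?** Inputs: 50 families required and 16 % attrition (Sample size and power analysis).

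- 50 / (1 − 0.16) = 59.5, rounded up to 60. This reproduces the stated target.
- 60 × 0.84 = 50.4 families with complete data.
- 60 × 0.16 = 9.6, or about 10 families without complete data.

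The 16 % covers dropout from all causes. The article gives no separate figure for active withdrawal and none for reasons, so about 10 families is the whole allowance and not an estimate of how many the rule would affect.

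**4. What bias could follow?** Let p be the proportion of an arm with missing later HbA1c. Let d be the amount, in SD, by which the unseen values are worse than the model predicts under missing at random. To a first approximation:

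bias in the arm contrast = p(INT) × d(INT) − p(CAU) × d(CAU)

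The documents give neither p nor d by arm, so the values below are assumptions. With 16 % missing in one arm and no loss in the other:

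- d = 0.25: 0.16 × 0.25 = 0.04 SD
- d = 0.5: 0.16 × 0.5 = 0.08 SD
- d = 1.0: 0.16 × 1.0 = 0.16 SD

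With half that loss (8 % of one arm), the figures are 0.02, 0.04 and 0.08 SD. With equal p and equal d in both arms the two terms cancel and the bias is about 0. For scale, the trial is designed around an effect size of 0.5.

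**5. What could be recovered?** The primary outcomes are all parent or child reports and cannot be collected once a family stops answering. The other part of metabolic control, blood glucose readings, is downloaded or copied at home visits and is lost with them. Among the outcomes as described, HbA1c is the one that can continue without contact with the family.

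**The case against.** The strongest reply is that stopping collection when a participant withdraws is ordinary consent practice. Access to the diabetes team is part of taking part, and taking part is voluntary. A child's clinical data cannot be assumed available after the parent has left. This is right, and it means that HbA1c may continue only if the family agrees. It does not explain why the family is not asked.

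A second reply is that this is a journal article and that withdrawal levels may be set out in a consent form or full protocol not shown. That is possible. The point does not rest on an omission, however: the article states a rule without exception, and as worded that rule excludes a middle option.

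Third, the missing-data section already makes the validity of FIML conditional, and a sensitivity analysis may sit in an analysis plan not shown. That also stands, and no fault is claimed there.

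A reader might infer more than the text supports:

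- That withdrawn families drop out of the intention-to-treat comparison. They do not: Statistical analyses and Missing outcome data keep every randomised family in, with earlier data. The withdrawal rule and the intention-to-treat statement do not contradict each other.
- That they drop out of the safety record. Nothing removes events reported before withdrawal, and the article describes no safety comparison that could be biased.
- That families leave because things get worse, or for different reasons in the two arms. Participants are not blinded, and only care-as-usual families have the programme still to come after the 6-month assessment, so this is conceivable. The article gives no numbers or reasons to show it.

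**Conclusion.** The point holds in a narrow form. As worded, the rule ends collection of HbA1c that could be obtained without study contact, and FIML is unbiased for that loss only under missing completely at random or missing at random. This is a cheap improvement to a stated rule, not an error that undermines the trial.

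The size of any bias is unknown. The range of 0.04 to 0.16 SD assumes that the full 16 % falls in one arm, that all of it is active withdrawal, and that the unseen values are worse by 0.25 to 1.0 SD than predicted. Less loss, or loss balanced between the arms, gives less, down to about zero. The primary outcomes are unaffected by the proposed change.

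**What to change.** Replace the Recruitment sentence with a two-way choice. A family that wishes to stop is asked whether it:

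- withdraws only from questionnaires, sessions and home visits, with routine HbA1c still obtained from the diabetes team if it agrees; or
- withdraws fully, after which nothing more is collected.

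Record the choice, its date and any reason offered, and report these by arm. Include the retained HbA1c values in the intention-to-treat analysis in the same way as those of other families.

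The cost is consent-form wording and a minor ethics amendment, for which the Ethics section already provides a route. No extra visit is needed. The gain is partial: some families will choose full withdrawal, and only one secondary outcome benefits.
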